### Follow-up

Tumor regression should be evaluated according to RECIST Version 1.1 within 1–2 month after completion of treatment and rates of cCR and cPR should be documented. All patients should be followed up for at least 5 years after completion of the protocol and the time interval is every 3 months for the first 2 years, every 6 months for 3–5 years and once a year after 5 years.

Every follow-up should include: a. History-taking: symptoms of cough, fever, hoarseness, dysphagia or chest tightness, etc. b. Blood routine, basic metabolic panel, tumor markers, etc. c. Contrast enhanced CT of neck, thorax and abdomen, ultrasound of neck and abdomen, upper gastrointestinal contrast, bone scan (in case of bone pain or abnormally-elevated alkaline phosphatase), CT or MRI of brain (in case of any symptoms related to central nervous system), etc. d. Documentation of patients’ status of survival, disease progression, subsequent treatment, nutrition, life quality and late toxic effects, etc.

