#### CGA

As mentioned before, due to the specialty of elderly population, enrolled patients will receive a comprehensive assessment called CGA (including social support, general status, body function, nutritional status, mental health, cognitive ability and so forth) both before and after treatment. Detailed procedures of CGA are listed in Table 1.

**Table 1 Tab1:** Domains and measures accessed by CGA before and after treatment

Domain with measure	No. of items	Range of score
Quality of life and specific module for EC		
EORTC QLQ-C30 (Version 3.0) [34]	30	30–126
QLQ-OES-18 [35]	18	18–72
Functional status		
ECOG performance status [36]		0–5
Karnofsky performance status [37]		0–100
Activities of daily life (Barthel index) [38]	10	0–100
Instrumental activities of daily life (Lawton’s) [39]	8	0–5/8
Comorbidity		
Charlson comorbidity index [40]	19	0–37
Cognitive status		
Mini Mental State Examination [41]	11	0–30
Psychological status		
Geriatric depression scale-5 items [42]	5	0–5
Nutritional status		
Body mass index [43]		
Mini-nutritional assessment [44]	18	0–100
Social support		
Medical Outcomes Study - social support survey [45]	20	20–100

*CGA* comprehensive geriatric assessment, *EC* esophageal cancer, *ECOG* Eastern Cooperative Oncology Group, *EORTC* The European Organization for Research and Treatment of Cancer, *MOS* Medical outcomes study

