### Chemotherapy

S-1 will be orally taken twice daily (or through nasal feeding tube for patients with enteral nutrition) within half an hour after meals during treatment days. It should not be taken during weekends or whenever radiotherapy is interrupted or stopped. The specific dosage for each patient is calculated according to body surface area in Table 2:

**Table 2 Tab2:** Relationship between body surface area and dose of S-1

Body surface area (m^2^)	Initial dose
<1.25	40 mg, bid
≥1.25~<1.50	50 mg, bid
≥1.5	60 mg, bid

Generally, 4–8 weeks are needed for patients to recover after completion of SIB + S-1 (status of food intake, physical capacity, biochemical tests, etc.). Four cycles of S-1 will be given to those eligible for consolidation chemotherapy. Treatment schedule for patients in both arms is shown in Fig. 3. The daily-dose of consolidated S-1 is the same as that of concurrent phase, but it will be administered for the first 2 weeks on each 21-days cycle. Blood routine should be monitored every week and hepatic and renal functions every cycle during chemotherapy.

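### The 3-monthly follow-up clock starts at protocol completion, which comes 16–20 weeks later for SIB + S-1 patients who finish consolidation and exposes PFS to bias in that arm's favour

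*Protocol article*

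**What the plan says.** All references are to the protocol article.

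- **Follow-up, visits.** Patients are to be seen over five years or more "after completion of the protocol and the time interval is every" three months in years one and two. Each visit includes contrast-enhanced CT and documents "status of survival, disease progression, subsequent treatment, nutrition, life quality and late toxic effects".
- **Follow-up, response.** "Tumor regression should be evaluated according to RECIST Version 1.1 within 1–2 month after completion of treatment".
- **CGA.** The geriatric assessment, whose Table 1 includes the EORTC QLQ-C30 and QLQ-OES-18, is done "both before and after treatment", with no week given.
- **Chemotherapy.** "Generally, 4–8 weeks are needed for patients to recover after completion of SIB + S-1". Then: "Four cycles of S-1 will be given to those eligible for consolidation chemotherapy". Each cycle lasts 21 days, with S-1 in the first two weeks.
- **Toxicity and adverse events.** Suitability for consolidation is looked at again 4–8 weeks after radiotherapy. No tumour imaging is mentioned there.
- **Study design and objectives.** The secondary objectives are progression-free survival, recurrence-free survival, failure pattern, toxicity and quality of life. The primary objective is 1-year overall survival.

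**The concern.** Completion of the protocol is not the same moment in the two arms. A SIB patient completes it at the end of radiotherapy; a SIB + S-1 patient who receives the full assigned regimen completes it after consolidation. A visit schedule counted from that date looks for progression at different times since randomisation.

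Progression that shows only on imaging is dated when someone looks. If the first 3-monthly scan comes months later in one arm, progression in the meantime is recorded late there, and that arm's PFS and recurrence-free survival look longer without any treatment effect. The direction is predictable and favours the experimental arm, in an open trial. Quality of life recorded at these visits is likewise taken at different times since radiotherapy, so treatment is mixed with recovery time.

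**Working it through.** **Step 1. Length of treatment, in weeks from the start of radiotherapy** (the delay from randomisation is assumed equal in both arms).

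- Radiotherapy, five fractions a week: 28 / 5 = 5.6 weeks in both arms (junctional tumours: 25 / 5 = 5.0).
- SIB + S-1 only, recovery plus four 3-week cycles: 4 + 4 × 3 = 16 to 8 + 4 × 3 = 20 weeks. To the last S-1 dose: 4 + 3 × 3 + 2 = 15 to 8 + 3 × 3 + 2 = 19 weeks.
- Completion: week 5.6 (SIB) against 5.6 + 16 = 21.6 to 5.6 + 20 = 25.6 (SIB + S-1, all four cycles).

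**Step 2. First 3-monthly visit (13 weeks after completion).**

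- SIB: 5.6 + 13 = week 18.6.
- SIB + S-1: 21.6 + 13 = 34.6 to 25.6 + 13 = week 38.6.

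A 6-month (26-week) landmark thus falls after the first such visit in one arm and before it in the other.

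**Step 3. Response evaluation, under each reading of completion** (1–2 months taken as 4.3–8.7 weeks).

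- End of all assigned treatment: weeks 9.9–14.3 (SIB) against 25.9–34.3 (SIB + S-1).
- End of the concurrent phase: weeks 9.9–14.3 in both arms.

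**Step 4. Effect on PFS when there is no true difference.** The document gives no PFS figure, so these inputs are assumptions: exponential PFS, median 6, 9 or 12 months; 25% of events are deaths, dated exactly; other events found at a scan 6 weeks after completion and every 13 weeks thereafter, unless found clinically; data cut 52 weeks after the last patient. From the document: 150 patients per arm, accrual of 130 weeks (2.5 years), one-sided 5% test (log-rank).

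| Scenario | Apparent HR (6 / 9 / 12 months) | One-sided rejection |
|---|---|---|
| All finish four cycles, scan-only detection | 0.82 / 0.90 / 0.93 | about 46% / 20% / 12% |
| All finish, half of progressions found clinically | 0.92 / 0.96 / 0.97 | 15% / 9% / 7% |
| 60% finish, half found clinically | 0.96 to 0.98 overall | about 7% to 9% |

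The top row takes every visit at a fixed week and the response scan as counted from the late completion date too. If that scan falls at the same week in both arms, the bias is smaller.

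**Step 5. A second set of assumptions.** Here death competes with progression before detection (median death 84 weeks, median progression 40–80 weeks), the dates of completion and of the response scan are spread across their windows, all patients finish four cycles, and 0–50% of progressions surface clinically. The implied PFS medians are 40 × 84 / (40 + 84) = 27.1 weeks and 80 × 84 / (80 + 84) = 41.0 weeks. The apparent HR is 0.95–0.99 and rejection about 5–12%. Median PFS hardly moves (31.7 against 32.4 weeks in the first case below), but 6-month PFS does:

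- Median progression 40 weeks, scan-only: 58.5% (SIB) against 80.6% (SIB + S-1), a difference of 22.1 points.
- Median progression 80 weeks, half found clinically: 67.3% against 73.1%, a difference of 5.8 points.

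**The case against.** **Completion is undefined.** The Chemotherapy section uses the word for the end of the concurrent phase, and the 4–8 week recovery nearly coincides with the 1–2 month response window. The response evaluation may therefore be meant for before consolidation, at the same time in both arms. This stands, and Fig. 3, which is not shown, might settle it. It reaches the 3-monthly visits less well: they are counted from completion of the protocol, and consolidation is part of the assigned treatment in the title and the design section.

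**The gap is a ceiling.** Consolidation is only for eligible patients and S-1 has stopping rules, so some patients have a smaller shift or none. This stands. It also means that the anchor varies with tolerance inside the SIB + S-1 arm.

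**The large figures are a pessimistic corner.** A 6-month median implies 0.5² = 25% PFS at one year, beside planned 1-year survival of 65% and 75%. Regular blood monitoring brings patients into contact with the site during consolidation, so some progression would surface clinically. This stands for the size, not for the direction.

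**The detailed calendar and the PFS time origin belong in the full protocol or analysis plan.** Agreed; neither is counted as missing here. The point is the anchor that the article does state.

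A reader might infer that all secondary endpoints are biased, or that response and CGA are compared at about 3 against 7 months. The documents do not support that. Response and CGA are not listed secondary objectives, their timing is ambiguous, and toxicity recording is not tied to completion.

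**Conclusion.** The point holds for the 3-monthly visits. On the plain reading, scheduled imaging and quality-of-life recording start 16–20 weeks later in SIB + S-1 patients who complete consolidation, and no tumour imaging is stated during the consolidation cycles. PFS and recurrence-free survival are exposed to bias favouring that arm, most at early landmarks, and quality of life is recorded at unequal times since randomisation. The response evaluation and the post-treatment CGA share the problem only if completion includes consolidation.

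The schedule gap follows from the document's own figures. The size of the PFS bias does not: it depends on median PFS, uptake of consolidation, how progression is detected and how scan dates spread. The whole-curve effect may be modest, and the milder scenarios are close to nominal. A reader might take the worst case as the expected effect, but nothing in the document supports those inputs over the milder ones. Scan timing cannot affect 1-year overall survival, so the trial's main conclusion is not at risk. This is a cheap improvement.

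**What to change.** Count response imaging, 3-monthly imaging and the quality-of-life and CGA assessments in both arms from one common date, either randomisation or the end of radiotherapy, and place them at the same weeks. State that PFS is measured from randomisation. Replace the two uses of completion in the Follow-up section with that date, so that the roughly 15 centres read it alike.

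The cost is one amendment to the visit schedule. A scan or two in the SIB + S-1 arm would fall during consolidation. No new type of procedure is needed, and neither the sample size nor the treatment changes.

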### Statistical analysis & sample size considerations

We assume that an estimated difference in 1-y OS of 65% (SIB arm) versus 75% (SIB + S-1 arm) would justify applying this regimen in the future. Assuming a one-sided significance level of 0.05, a power of 0.80, and 10% of lost in each arm, a total of 300 patients would be needed in this trial.

Estimates of median OS will be based on the Kaplan-Meier method and log-rank tests will be used to determine the significance. Cox regression analysis will be conducted to identify prognostic factors for survival benefit, which will be used in adjusted analyses of the treatment effect.

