**Methods/design:**

The study is a two arm, open, randomized multicenter Phase III trial with patients over 70 years old with stage IIA-IVB (UICC 2002, IVB only with metastasis to supraclavicular or celiac lymph nodes) squamous cell carcinoma or adenocarcinoma of esophagus or gastroesophageal junction. A total of 300 patients will be randomized using a 1:1 allocation ratio stratified by disease stage and study site. Patients allocated to the SIB arm will receive definitive SIB radiotherapy (95%PTV/PGTV 50.4Gy/59.92Gy/28f) while those randomized to SIB + S-1 arm will receive definitive SIB radiotherapy concurrent and consolidated with S-1. The primary endpoint of the trial is 1-year overall survival. Secondary objectives include progression-free survival, recurrence-free survival (local-regional and distant), disease failure pattern, toxicity profile as well as quality of life. Besides, detailed radiotherapy protocol and quality assurance procedure have been incorporated into this trial.

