## Methods/design

### Study design and objectives

This study is an open, multicenter Phase III clinical trial. Approximately 15 participating centers throughout China are involved. The technique of SIB is adopted in this study with a dose of 50.4Gy/2.14Gy/28f to planning target volume (PTV) and 59.92Gy/2.14Gy/28f to planning gross tumor volume (PGTV). S-1 is given both concurrent with and after radiotherapy. Patients enrolled are stratified by disease stage and study site and assigned to either SIB + S-1 group or SIB group using a 1:1 allocation ratio at randomization. A flow chart giving an overview of the study design is shown in Fig. 1.

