**Fig. 1 Fig1:**
[figure not shown]
Flow chart of 3JECROG P-01

The primary objective of this trial is to compare the 1-year OS of SIB + S-1 group with SIB group. Secondary objectives include progression-free survival, recurrence-free survival (local-regional and distant), disease failure pattern, toxicity profile as well as quality of life.

The study started on February, 2017 and the duration of inclusion will be approximately 2 and a half years.

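### The primary endpoint is 1-year overall survival, but the only named test is a log-rank test and the only named survival estimate is the median; neither targets survival at 12 months

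*Protocol article*

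**What the plan says.** The abstract of the protocol article states: "The primary endpoint of the trial is 1-year overall survival". The section Study design and objectives repeats it as the objective: "The primary objective of this trial is to compare the 1-year OS of SIB + S-1 group with SIB group".

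The section Statistical analysis & sample size considerations sets the target effect as 65% alive at 1 year with SIB alone against 75% with SIB + S-1. The design inputs follow: "Assuming a one-sided significance level of 0.05, a power of 0.80, and 10% of lost in each arm, a total of 300 patients".

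The same section then names the analysis: "Estimates of median OS will be based on the Kaplan-Meier method and log-rank tests will be used to determine the significance". One further analysis is named: "Cox regression analysis will be conducted to identify prognostic factors for survival benefit, which will be used in adjusted analyses of the treatment effect". No comparison of survival at 12 months is named.

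Inclusion is to last about two and a half years. The Follow-up section says "All patients should be followed up for at least 5 years after completion of the protocol".

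**The concern.** A comparison of 1-year OS asks what fraction of each arm is alive at one point in time. A log-rank test compares the two survival curves over whatever period the data cover, and the median is read off wherever a curve crosses 50%. The article labels the first as primary and names tools for the second.

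The two agree in substance only if the hazard ratio is constant. That is not assured here. Under Chemotherapy, S-1 is given with radiotherapy, then after a 4 to 8 week recovery, for four 21-day cycles, so the arms differ in treatment early on and not later.

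At stake is what a positive or negative result would mean. A log-rank result reported as the verdict on 1-year OS could be positive with no difference at 12 months, or negative with a true 12-month gain of the size that the protocol says would justify the regimen.

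**Working it through.** **Inputs from the article.** 1-year OS 65% and 75%; one-sided alpha 0.05 (z = 1.645); power 0.80 (z = 0.842); 300 patients, 1:1; 10% loss, so 270 evaluable, 135 per arm; accrual 2.5 years.

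**Assumptions.** Exponential survival unless stated, uniform accrual, lost patients contributing nothing. The article gives no follow-up time for the primary analysis, so a range is shown.

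**1. Where the medians fall.** Yearly hazards are −ln 0.65 = 0.4308 and −ln 0.75 = 0.2877. Medians are 12 × ln 2 / hazard = 19.3 and 28.9 months. Estimating them needs data beyond 12 months. The hazard ratio is 0.2877/0.4308 = 0.668.

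**2. Does 300 follow from a comparison of two 1-year rates?**

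- n per arm = [1.645√(2 × 0.70 × 0.30) + 0.842√(0.65 × 0.35 + 0.75 × 0.25)]² / 0.10² = (1.066 + 0.542)² / 0.01 ≈ 259.
- Total 518; with loss 518/0.9 = 576. So no.
- Power with 135 per arm: Φ[(0.10√135 − 1.066)/0.644] = 56%. With 150 per arm: 60%.
- A log-rank test censored at 12 months does no better: 270 × 0.30 = 81 deaths give 57% power, and 300 × 0.30 = 90 deaths give 61%.

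**3. Does 300 follow from a log-rank design?**

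- Schoenfeld: 4(1.645 + 0.842)² / (ln 0.668)² = 152 deaths. Freedman: (1.645 + 0.842)² × [(1 + 0.668)/(1 − 0.668)]² = 156 deaths.
- Proportion dead with follow-up F after last entry: 1 − [exp(−hF) − exp(−h(2.5 + F))]/(2.5h), averaged over the arms.

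| F assumed (years) | Proportion dead | N with loss, Schoenfeld / Freedman |
|---|---|---|
| 1.0 | 0.534 | 317 / 325 |
| 1.1 | 0.550 | 308 / 316 |
| 1.2 | 0.565 | 300 / 308 |
| 1.3 | 0.580 | 293 / 300 |
| 1.4 | 0.594 | 285 / 293 |
| 5.0 | 0.880 | 192 / 197 |

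So 300 fits a log-rank design if roughly 1.1 to 1.4 years of follow-up after last entry is assumed. It does not follow from the stated inputs alone.

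**4. Can the two tests give different verdicts?** Simulation with 135 per arm, one-sided 0.05 and 2.5-year accrual. The 12-month test is the Kaplan-Meier difference with Greenwood variance. Scenarios B and C are assumed.

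| Scenario | Log-rank significant, 1 y after last entry | Log-rank significant, 5 y | 12-month test |
|---|---|---|---|
| A. Proportional hazards, 0.668 | 78% | 93% | about 56% |
| B. 65% vs 75% at 1 year, equal hazards afterwards | about 35% | about 27% | about 56% |
| C. Equal 1-year OS, hazard ratio 0.668 afterwards | about 23% | about 61% | about 5% |

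Repeat runs differ by one or two points (36% and 28% in B, 25% and 59% in C), which is simulation error. Even in A the two tests disagree on significance in about 27% of trials at 1 year and 36% to 39% at 5 years.

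**The case against.** The strongest defence is that the endpoint is loosely worded and the test is the right one. Under proportional hazards, 65% against 75% at 1 year and a hazard ratio of 0.668 are the same hypothesis. The sample size fits a log-rank design and is far from the 576 that two proportions need. A Kaplan-Meier analysis also yields the 1-year estimates directly. This stands as the most coherent reading of the design. It does not remove the mismatch: the article names 1-year OS as endpoint and as objective, and on that label the stated 80% power does not hold.

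A reader might infer several stronger points that the document does not support:

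- **That the log-rank is the only planned analysis.** Cox and adjusted analyses of the treatment effect are also planned, although they do not target 12 months either.
- **That the log-rank will run over five or more years.** The five years are a patient follow-up schedule, not the time of the primary analysis. The use of data beyond 12 months is inferred from the planned median.
- **That the absent data cut-off or number of deaths is a fault.** A condensed article may leave this to the full protocol or analysis plan, and nothing suggests that it will be chosen after seeing data.
- **That rising log-rank power with more deaths is a defect.** Any log-rank test behaves this way.
- **That a log-rank win in scenario C is a false positive.** It would be a true survival benefit, but not one at 12 months.

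The 12-month test is also no safeguard: it misses a true gain of the planned size in about 44% of trials.

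**Conclusion.** The mismatch is real and lies in what the article states, not in what it omits: a fixed-time primary endpoint is paired with a whole-curve test and a median. It is not shown that the log-rank test is wrong or that 300 patients is the wrong number. Under proportional hazards the design is coherent as an OS log-rank trial with the wrong endpoint label.

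The consequence depends on the hazards. For a gain confined to year 1, the log-rank has about 27% to 35% power where a 12-month test has 56%. For a purely later gain, it is significant in about 23% to 61% of trials where a 12-month test stays near 5%. These figures rest on the assumed scenarios, 270 evaluable patients and follow-up of 1 or 5 years after last entry. If 1-year OS is truly primary, power at the planned size is about 56% to 60%, not 80%.

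**What to change.** Choose one target by amendment, before outcome data are seen, and use the same wording in the abstract, the objectives and the statistical section.

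- **Option (a): OS as primary.** Define the primary endpoint as overall survival compared by log-rank, analysed at about 152 deaths (Schoenfeld; 156 by Freedman) for 80% power at one-sided 0.05. State the follow-up assumption behind 300 patients, about 1.1 to 1.4 years after last entry. Report the Kaplan-Meier 1-year difference with its confidence interval as the key supporting estimate.
- **Option (b): 1-year OS as primary.** Test the Kaplan-Meier difference at 12 months (Greenwood variance) once all patients have 12 months of follow-up, and make the log-rank secondary. Restate the power as about 56% with 135 per arm to 60% with 150 per arm. Restoring 80% would need 576 patients with 10% loss.

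Neither option needs new data items. Option (a) changes the primary endpoint label of a trial that has been recruiting since February 2017, so the amendment should be dated and justified. Option (b) keeps the label and costs the stated power. Option (a) fits the planned sample size better.

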### Patient

#### Patient selection

Patients older than 70 years old with histocytologically proven stage IIA-IVB (UICC 2002, IVB only with metastasis to supraclavicular or celiac lymph nodes) inoperable squamous cell carcinoma (SCC) or adenocarcinoma (AC) of esophagus or gastroesophageal junction are eligible for recruitment. No other treatment is allowed before enrollment. For cancer of esophagogastric junction, the center of the tumor could not extend 2 cm into the gastric cardia. Patients must have adequate hematological, renal and hepatic functions defined as: neutrophils ≥3.5 × 10^9^/L, granulocytes ≥1.5 × 10^9^/L, platelets ≥100 × 10^9^/L, urea nitrogen (BUN) ≤ 1.0 × upper normal limit (UNL), creatinine (Cr) ≤ 1.0 × upper normal limit (UNL), alanine aminotransferase (ALT), aspartate aminotransferase (AST) ≤1.5× UNL; alkaline phosphatase (ALP) ≤ 1.5× UNL; total bilirubin ≤UNL. General condition of enrolled patients must be acceptable (i.e. Karnofsky Performance Status≥70 or Eastern Cooperative Oncology Group performance status ≤1, Charlson Comorbidity Index≤3).

Exclusion criteria include prior malignancies (other than curable non-melanoma skin cancer or in situ cervical cancer) within 5 years, distant lymph node (other than metastasis to supraclavicular or celiac lymph nodes) or visceral metastasis (including metastasis to bone, lung, liver, pleura or peritoneum, etc.), uncontrolled infection such as tuberculosis or hepatitis, uncontrolled hypertension or diabetes, severe comorbidities such as myocardial infarction, cerebral embolism or serious arrhythmia within 6 months, obvious sign of esophageal perforation or deep ulcer affirmed by barium esophagram.

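### Randomisation is stratified by stage and site, but stage has no assured place in any treatment comparison; if run without strata the log-rank test stays valid and may lose roughly 0 to 5 points of power

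*Protocol article*

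**What the plan says.** Under Study design and objectives, the protocol article states: "Patients enrolled are stratified by disease stage and study site and assigned to either SIB + S-1 group or SIB group using a 1:1 allocation ratio". The Abstract says the same. On the number of sites: "Approximately 15 participating centers throughout China are involved". Under Patient selection, the eligible disease is "histocytologically proven stage IIA-IVB (UICC 2002, IVB only with metastasis to supraclavicular or celiac lymph nodes"), so several stage groups are admitted. How many stage levels the randomisation uses is not given.

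Under Statistical analysis & sample size considerations, the only significance test named is the log-rank: "log-rank tests will be used to determine the significance". No strata are attached, and the words stratified and unstratified do not appear there. The next sentence plans Cox regression to find prognostic factors and then uses those factors to adjust the treatment comparison. It names neither stage nor site. The design target is "an estimated difference in 1-y OS of 65% (SIB arm) versus 75% (SIB + S-1 arm"), with this specification: "Assuming a one-sided significance level of 0.05, a power of 0.80, and 10% of lost in each arm".

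**The concern.** Stratified allocation balances stage between the arms. The analysis benefits fully only if it also conditions on stage. When stage is prognostic and allocation is balanced on it, an unstratified log-rank test uses a variance that is too large for the design, so it rejects a little less often than its nominal level. The hazard ratio averaged over stages also lies closer to 1 than the within-stage hazard ratio. Both effects lower power.

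The adjusted analysis does not close the gap. Its stated rule takes covariates from what the trial's own data identify. A factor fixed at randomisation might or might not enter, while factors chosen after outcomes are seen will. At stake are a few points of power in a trial planned for only 0.80, and an adjusted hazard ratio whose covariates are not known in advance.

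**Working it through.** **Inputs from the protocol article.** 1-year OS 65% versus 75%; one-sided alpha 0.05; power 0.80; 10% loss per arm; 300 patients; accrual about 2.5 years; about 15 sites; 1:1 allocation stratified by stage and site.

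**Assumptions (not in the documents).** Exponential survival with proportional hazards; time of analysis; number of stage levels; hazard ratio between stages; variation between sites.

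**The plan's own figure.** HR = ln(0.75)/ln(0.65) = 0.668. Schoenfeld events = 4 × (1.645 + 0.842)² / (ln 0.668)² = 152; Freedman's formula gives 156.

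The probability of death in an arm with hazard λ, accrual a and minimum follow-up f is 1 − (e^(−λf) − e^(−λ(f+a)))/(λa). With a = 2.5 and f = 1.25 years this averages about 0.57 over the arms. So 152 events need 266 patients, and 266/0.9 gives 296 (Freedman: 304). With f = 1 year the totals are 317 and 326. The stated 300 therefore matches a log-rank calculation only with an unstated follow-up of about 1.25 years. That is a separate matter; here it shows only that there is little power to spare.

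**Simulation of the choice of strata.** 6,000 trials per setting; 300 patients; 15 unequal sites; blocks of 4 within strata; three stage levels; site log-hazard SD 0.2; minimum follow-up 1 year; one-sided 0.05. Power:

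| HR per stage step | No strata | Stage | Site | Stage × site | Stage minus none (points) | Stage × site minus none (points) |
|---|---|---|---|---|---|---|
| 1.0 | 0.792 | 0.789 | 0.774 | 0.734 | −0.3 | −5.8 |
| 1.3 | 0.779 | 0.785 | 0.754 | 0.728 | +0.6 | −5.1 |
| 1.6 | 0.769 | 0.790 | 0.747 | 0.732 | +2.1 | −3.7 |
| 2.0 | 0.745 | 0.797 | 0.722 | 0.734 | +5.2 | −1.1 |

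The Monte Carlo standard error of a power is about √(0.79 × 0.21/6000) = 0.005. As a check on the first row, Schoenfeld's formula at 1 year of minimum follow-up gives 0.78 for 270 patients and 0.82 for 300.

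Type I error in the same order of stage effects:
- No strata: 0.0507, 0.0522, 0.0428, 0.0365.
- Stage strata: 0.0500, 0.0543, 0.0507, 0.0475.

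The standard error here is about √(0.05 × 0.95/6000) = 0.003. The unstratified test is at nominal when stage matters little and below it when stage matters more.

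**Other settings.**
- 2,000 trials per setting with site SD 0 or 0.3: stage strata changed power by −0.7 to +6.2 points against no strata.
- 4,000 trials of 270 patients with a 30/45/25% stage mix: 75.5% without strata versus 77.3% with stage strata at stage hazard ratios 1:1.5:2.25 (+1.8), and 71.3% versus 76.3% at 1:2:4 (+5.0). Type I error without strata was 4.1 to 4.4%.
- A further simulation: 0.80 without strata versus 0.79 with stage strata when stage has no effect (−1), and 0.76 versus 0.80 at a hazard ratio of 2 per step (+4).

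**Why not both factors.** With three stage levels, 15 sites give 15 × 3 = 45 cells, or 300/45 = 6.7 patients and 152/45 = 3.4 deaths per cell. A death contributes nothing when only one arm is still at risk in its cell. Crossed strata had lower power than no strata in every setting above where both were run except one (0.737 versus 0.732, stage step 2.0 and site SD 0.3). They were below stage-only strata in all of them.

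**The case against.** The strongest reply is that the article never says the test is unstratified. A stratified log-rank test is still a log-rank test, and a condensed article may leave the strata to the full protocol or analysis plan, which are not shown. This stands: a reader might infer that an unstratified test has been chosen, and the text does not support that. What is stated, and is more than missing detail, is the covariate rule. Adjustment relies on factors the data identify, so the factors used at randomisation are not assured a place.

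It can also be said that a strongly prognostic stage would probably be picked up by the Cox step. That is likely, but not guaranteed, and it would not alter the log-rank test that determines significance.

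The magnitude rests on assumed stage effects. Eligibility is limited to inoperable disease with restricted IVB, which may narrow the prognostic range. A 5-point loss needs a hazard ratio of about 2 per step, a fourfold spread over three levels; at 1.3 per step the loss is under 1 point. This stands too, and is why the size is given as a range starting at about zero.

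Two further inferences fail. One is that ignoring the strata invalidates the result: type I error is not inflated, so the risk is a missed effect and not a false claim. The other is that every randomisation factor belongs in the test: adding site as a stratum, alone or crossed with stage, generally costs power.

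**Conclusion.** The point holds as a modest one. The documents stratify allocation by stage, name no strata for the test that decides significance, and choose adjustment factors from the data. If the test is run without strata, validity is kept and the likely cost is roughly 0 to 5 points of power against a stage-stratified test. It is near zero if stage is weakly prognostic, and about 5 points (between 4 and 6 across the simulations) at a hazard ratio of 2 per stage step. These figures assume proportional hazards, three stage levels and about 1 year of minimum follow-up.

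The documents do not show that the strata are discarded, that an unstratified test is fixed, or that using site strata would recover power. Nor would stage stratification settle the separate question of how 300 patients was derived.

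**What to change.** State in the protocol and analysis plan, before outcome data are analysed:

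- The primary log-rank test is stratified by the stage grouping used at randomisation, with the levels listed, and by nothing else.
- The hazard ratio and its interval come from a Cox model stratified by the same grouping.
- Stage enters the adjusted model whatever the data-driven selection finds.
- Site is examined in a sensitivity analysis, for example with a shared frailty or with small sites pooled.
- The unstratified log-rank test is reported as a sensitivity analysis.

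If the full protocol or analysis plan already names stage as the stratum, it is enough to align the text. The cost is a sentence or two, and no new data are needed because stage must be known at randomisation. The statistical downside is at most about 1 point of power if stage turns out not to be prognostic.
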